### Study design

This is a multicenter open-labelled, controlled, randomized clinical trial, designed to test the effects of the buffer substance in biocompatible PD fluids on peritoneal small solute transport capacity. All subjects will undergo a 2-month run-in period, in which they receive conventional lactate buffered, acidic, GDP containing PD fluid. During this period, patient eligibility for the trial will be verified and the dialysis dose will be optimized if necessary to ensure appropriate PD adequacy. At the end of this period, the patients will be stratified according to residual renal function (greater or less than 100 ml urine output/day/1.73 m^2^) and the type of phosphate binder therapy (Sevelamer vs. calcium-containing phosphate binders), since these variables may affect the overall efficacy of metabolic acidosis control. Following stratification, subjects will be randomized centrally to receive either the lactate-containing Balance solution or the bicarbonate buffered Bicavera^® ^solution for a period of 10 months. Both during the run-in period and during the intervention phase, patients will be monitored by monthly clinical and laboratory examinations, including capillary blood gas analyses. In addition, peritoneal equilibration tests (PETs), 24-hour dialysate and urine collections and intraabdominal pressure assessments will be performed at time of randomization (with conventional PD fluid) and after 3, 6 and 10 months of treatment (with the study solutions). Also, peritoneal biopsies will be performed on occasion of intraabdominal sugery or laparoscopy prior to start and after termination of the study (usually at time of catheter insertion and renal transplantation).

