### Secondary outcome measures

Secondary outcome measures will be surrogate parameters of mesothelial cell viability (CA-125), peritoneal neoangiogenesis (VEGF), fibrotic activity (TGF-β) and local inflammation (IL-6). With the same intention, the evolution of peritoneal histomorphology will be assessed in all patients available for sequential biopsies. Moreover, possible differential effects of lactate and bicarbonate buffer on the control of metabolic acidosis will be assessed by monthly blood gas analyses. Finally, the incidence and clinical course of peritonitis will be recorded as a possible indirect marker of local peritoneal macrophage function.

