### Exit criteria

Reasons for permanently discontinuing the study medication are 1) renal transplantation, 2) switch to hemodialysis due to PD technique failure, 3) patient/parent withdrawal of consent of participate, 4) patient moving out of the area to a location with no participating center within reasonable distance, and 5) a severe adverse event.

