### Clinical safety monitoring

An adverse event is defined as any untoward medical occurence in a patient who takes the study medication. It does not necessarily have a causal relationship with this treatment. This may be an unfavourable and unintended sign, symptom or disease, which is observed after exposure to the study medication, whether or not considered related to the treatment. Moreover, the participating investigators will report all treatment-emergent adverse events that are observed on the online adverse event form. This applies regardless of the clinical significance or the assessment of study drug causality. In this trial, such adverse events may include inflow pain, severe changes of the state of hydration, abnormal electrolyte and glucose blood levels, peritonitis, abdominal hernia, and allergic reactions.

A severe adverse event or reaction is any untoward medical occurrence that a) results in death, b) is life-threatening, c) requires inpatient hospitalization or prolonges an existing hospitalization, or d) results in persistent or significant disability/incapacity.

Any serious adverse event, whether or not considered related to the study medication, and any unexpected drug reactions with significant hazard to the patient population will be reported to the responsible safety assessor at Fresenius Medical Care by phone or by fax within 24 hours following first knowledge of the event. Alternatively the clinical monitor may be informed. This information will be forwarded to and evaluated by the safety monitoring committee, and reports of serious adverse reactions will be disseminated to all participating centers for submission to their respective institutional review boards. Fresenius Medical Care is responsible for passing on the information to relevant supervisory authorities.

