### Statistical approach

A computer based randomization protocol will be generated and applied centrally at the end of the run-in period. Baseline comparability between the two treatment groups will be evaluated with respect to entry criteria. Chi-square and t-tests will be used to assess differences between the two groups on the baseline variables. Any variables that are found to be discrepant between the two groups and that are related to the outcome variables will be treated as co-variates in later analyses.

In order to evaluate the patients' change in D/P_Cr _ratios, two strategies will be employed:

1. Repeated measure ANOVA will be performed on those patients who complete the 10-month observation period on the study medications.

2. The Kaplan-Meier method will be used to estimate the time in which patients are likely to display a ≥ 7.5 % increase in the D/P_Crea _ratio during the 10-month period. All patients started on study medication will be available for this analytical approach.

The same strategies will be used to analyze secondary outcome variables.

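### The blanket rule for secondary outcomes does not fit peritonitis or histology: the completer ANOVA leaves out children who exit through severe peritonitis or early transplantation, and neither strategy yields a peritonitis rate

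*Protocol article*

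**What the plan says.** The Statistical approach section sets two strategies for D/P creatinine.

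- Strategy 1: "Repeated measure ANOVA will be performed on those patients who complete the 10-month observation period on the study medications".
- Strategy 2: "The Kaplan-Meier method will be used to estimate the time in which patients are likely to display a ≥ 7.5 % increase" in that ratio. Its analysis set is wider: "All patients started on study medication will be available for this analytical approach".

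The section then closes with "The same strategies will be used to analyze secondary outcome variables", and makes no exception.

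Two of the secondary outcomes are peritonitis and histology.

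- **Peritonitis.** The Secondary outcome measures section says that "the incidence and clinical course of peritonitis will be recorded as a possible indirect marker" of macrophage function. The abstract says that both its rates and its severity will be analysed.
- **Histology.** The same section says that histomorphology is assessed in every patient who has sequential biopsies. The Study design section places these biopsies before the start and after the end of study, "usually at time of catheter insertion and renal transplantation".

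The Exit criteria section lists renal transplantation first, a switch to hemodialysis for technique failure second, and "5) a severe adverse event" last. The Clinical safety monitoring section defines such an event to include one that "requires inpatient hospitalization or prolonges an existing hospitalization", and names peritonitis among the possible adverse events.

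**The concern.** Peritonitis is a recurrent event observed over unequal follow-up. The article promises its rate and its severity, but the sentence on secondary outcomes assigns it two methods that give neither. Strategy 1 also selects its patients partly on the outcome: a child whose episode leads to admission, or ends in technique failure, stops study fluid and so is not a completer. The episodes most relevant to severity are the ones most likely to be left out.

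For histology the problem is a contradiction about the analysis set. One section takes all patients with sequential biopsies, and the other takes only 10-month completers. Transplantation is both the usual occasion for the second biopsy and an exit reason, so the two sets differ for exactly the children transplanted early.

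At stake are two secondary comparisons: an understated burden of peritonitis with a possibly distorted contrast between arms, and lost biopsy pairs in a small trial.

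**Working it through.** **1. Size of the completer set.** The Sample size estimation section enrols 60 and assumes 50% drop-out, so 60 × 0.5 = 30 children are expected outside strategy 1. The split by reason is not given. The number lost through early transplantation therefore lies between 0 and 30, and only those among them with a first biopsy would contribute a lost pair.

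**2. Person-time outside strategy 1.** Assume a constant exit hazard h that gives 50% drop-out at T = 10 months.

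- h = ln 2 / 10 = 0.0693 per month, or 0.832 per year.
- Mean follow-up = (1 − 0.5)/0.0693 = 7.21 months.
- Completers' share of person-time = 0.5 × 10 / 7.21 = 0.69.

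Even if no episode caused an exit, strategy 1 would use only about 69% of the observed follow-up and episodes.

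**3. Absolute rate when some episodes cause exit.** Let λ be the true rate per year and q the share of episodes that lead to exit. The article gives neither, so the values below only illustrate. Exits through peritonitis come on top of the 50% for other reasons.

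- Rate seen in completers = λ(1 − q), because no completer has had an exit-causing episode.
- Probability of completing: S = exp[−(h + λq)T], with T = 10/12 year.
- Mean follow-up: E = (1 − S)/(h + λq).
- Share of all observed episodes that strategy 1 uses = (1 − q)·T·S / E.

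Example with λ = 0.6 and q = 0.5: h + λq = 1.132, S = 0.389, E = 0.540 year, share = 0.5 × 0.833 × 0.389 / 0.540 = 0.30.

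| q | Completer rate ÷ true rate | Share of episodes used, λ = 0.3 | λ = 0.6 | λ = 1.0 |
|---|---|---|---|---|
| 0 | 1.00 | 69% | 69% | 69% |
| 0.25 | 0.75 | 50% | 48% | 46% |
| 0.50 | 0.50 | 32% | 30% | 27% |
| 0.75 | 0.25 | 16% | 14% | 12% |

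**4. Comparison between arms.** Take a true rate ratio of 2.0 (0.8 against 0.4 per year, assumed).

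- Equal q of 0.5: (0.8 × 0.5)/(0.4 × 0.5) = 2.0, so no distortion.
- q of 0.5 against 0.25: 0.40/0.30 = 1.33.
- q of 0.25 against 0.5: 0.60/0.20 = 3.0.

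A simulation in which children also differ strongly in underlying risk (gamma frailty, variance 1) gave completer ratios of 1.73, 1.08 and 2.98 for these three cases. The ratio of episodes to person-time in all patients, counting the exit-causing episode, stayed between about 1.8 and 2.0 in all settings run.

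**5. Strategy 2.** Its set is all patients started on study medication, so a first episode that triggers exit would be counted. Its difficulty is the event. The 7.5% threshold is stated for D/P creatinine and has no counterpart for an episode of infection. Read as time to first episode, the method gives neither a rate over recurrent episodes nor any measure of severity. For histology, one biopsy after the study yields no usable time to event.

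**The case against.** The strongest reply is that the sentence is shorthand. On this view *the same strategies* means a longitudinal analysis in completers plus a time-to-event analysis in all treated children, with outcome-specific events left to the full plan. The abstract already speaks of peritonitis rates, and the Secondary outcome measures section already names the wider biopsy set. Much of this stands, and it limits the point in four ways.

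- A reader might infer that peritonitis or biopsy is itself an exit. The Exit criteria section lists neither. Only peritonitis that counts as a severe adverse event, or ends in technique failure, is an exit. For biopsies the exit is transplantation, and a child who completes and is transplanted later stays in the set.
- A reader might infer that severe episodes vanish from every analysis. They do not, because strategy 2 covers all treated children.
- A reader might infer that the rule also spoils the analysis of CA-125, the other effluent markers or blood gases. The article ties the 7.5% rise to D/P creatinine, and these are continuous repeated measures for which a repeated-measures ANOVA is applicable. No error is shown there.
- A reader might treat peritonitis as the trial's main safety signal. The article calls it a possible indirect marker of macrophage function and requires all treatment-emergent adverse events to be reported separately.

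The reply does not save the sentence for the two outcomes at issue. The objection is not to a missing detail: the text assigns a method that cannot deliver the rates and severity promised in the abstract, and a patient set that contradicts the one given for histology.

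**Conclusion.** The sentence is wrong as written for peritonitis and histology, and for no other secondary outcome.

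For peritonitis, strategy 1 understates absolute incidence by the factor (1 − q) whenever some episodes cause exit, and leaves out the more severe ones. Distortion of the contrast between arms is conditional. With equal q a true ratio of 2.0 stays at 2.0 (1.73 under strong variation in risk). With q of 0.5 against 0.25, in one direction or the other, it becomes 1.33 or 3.0. Different admission decisions by arm are possible because the trial is open-label, but nothing in the article shows that they would occur. All values of λ and q are assumptions; only the 60 children, the 50% drop-out and the 10 months come from the article.

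For histology, the contradiction needs no assumption. The number of pairs lost cannot be calculated from the article.

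The change should be made. It concerns secondary outcomes and does not touch the primary analysis.

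**What to change.** Replace the closing sentence of the Statistical approach section, for these two outcomes, with the following.

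- **Peritonitis.** Episodes per patient-year in all randomised children, compared by negative binomial regression (or Poisson regression with robust standard errors) with log follow-up time as offset. State the period at risk, and count the episode that leads to exit. Summarise severity and clinical course over all episodes, including those that end study fluid.
- **Histology.** All sequential biopsy pairs, whether or not the child completed 10 months, with the time between biopsies taken into account. This brings the section into line with the Secondary outcome measures section.

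The clinical leads must also reconcile the Exit criteria and Clinical safety monitoring sections. The exit rule and the definition use *severe*, the reporting rule uses *serious*, and as printed any hospitalisation ends study fluid. Which rule is intended is for them to decide; the proposed analysis works under either.

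The cost is analysis wording and a clarification of terms. No new data are needed, apart from confirming that the episode that causes an exit is entered in the case report form.

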## Abstract

**Background:**

Peritoneal dialysis (PD) is the preferred dialysis modality in children. Its major drawback is the limited technique survival due to infections and progressive ultrafiltration failure. Conventional PD solutions exert marked acute and chronic toxicity to local tissues. Prolonged exposure is associated with severe histopathological alterations including vasculopathy, neoangiogenesis, submesothelial fibrosis and a gradual loss of the mesothelial cell layer. Recently, more biocompatible PD solutions containing reduced amounts of toxic glucose degradation products (GDPs) and buffered at neutral pH have been introduced into clinical practice. These solutions contain lactate, bicarbonate or a combination of both as buffer substance. Increasing evidence from clinical trials in adults and children suggests that the new PD fluids may allow for better long-term preservation of peritoneal morphology and function. However, the relative importance of the buffer in neutral-pH, low-GDP fluids is still unclear. In vitro, lactate is cytotoxic and vasoactive at the concentrations used in PD fluids. The BIOKID trial is designed to clarify the clinical significance of the buffer choice in biocompatible PD fluids.

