**Methods/design:**

The objective of the study is to test the hypothesis that bicarbonate based PD solutions may allow for a better preservation of peritoneal transport characteristics in children than solutions containing lactate buffer. Secondary objectives are to assess any impact of the buffer system on acid-base status, peritoneal tissue integrity and the incidence and severity of peritonitis.

After a run-in period of 2 months during which a targeted cohort of 60 patients is treated with a conventional, lactate buffered, acidic, GDP containing PD fluid, patients will be stratified according to residual renal function and type of phosphate binding medication and randomized to receive either the lactate-containing Balance solution or the bicarbonate-buffered Bicavera^® ^solution for a period of 10 months. Patients will be monitored by monthly physical and laboratory examinations. Peritoneal equilibration tests, 24-h dialysate and urine collections will be performed 4 times. Peritoneal biopsies will be obtained on occasion of intraabdominal surgery. Changes in small solute transport rates, markers of peritoneal tissue turnover in the effluent, acid-base status and peritonitis rates and severity will be analyzed.

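### The methods fixed for all secondary outcomes do not suit peritonitis: neither gives a rate over time at risk, and no planned analysis uses all episodes in all treated children

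*Protocol article*

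**What the plan says.** The protocol article, Statistical approach, names two strategies for D/P creatinine.

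- Strategy 1: "Repeated measure ANOVA will be performed on those patients who complete the 10-month observation period on the study medications".
- Strategy 2: "The Kaplan-Meier method will be used to estimate the time in which patients are likely to display" a rise of at least 7.5% in the ratio. For this one, "All patients started on study medication will be available for this analytical approach".

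The section closes with "The same strategies will be used to analyze secondary outcome variables" and makes no exception.

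Peritonitis is among those secondary variables. Objectives of the study lists its incidence and severity. Secondary outcome measures says that "the incidence and clinical course of peritonitis will be recorded as a possible indirect marker of local peritoneal macrophage function". The abstract (Methods/design) goes further and says that "acid-base status and peritonitis rates and severity will be analyzed".

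Three other sections bear on the point. Exit criteria lists "switch to hemodialysis due to PD technique failure" and a severe adverse event as reasons to stop study medication for good. Clinical safety monitoring names peritonitis as a possible adverse event and includes hospital admission in its definition of a severe one. Sample size estimation assumes that half of the 60 children drop out.

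**The concern.** D/P creatinine is measured at set visits, so a repeated-measures model and a time-to-threshold analysis are at least applicable to it. Peritonitis is a different kind of variable. A child may have none, one or several episodes, over a follow-up that ends early for half of the cohort. Its natural summary is episodes per patient-year, which is what the abstract announces.

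Under the stated rule, each method loses something different. The ANOVA is confined to completers, so an episode that ends treatment cannot enter it. Severity would then be compared only in children whose episodes did not take them off study fluid. A Kaplan-Meier analysis of the first episode does include the child who leaves, but it stops counting at that episode. The 7.5% threshold that defines the Kaplan-Meier event for D/P creatinine also has no stated counterpart for peritonitis severity.

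At stake is the secondary outcome that the protocol offers as its indirect marker of macrophage function and, through it, the Discussion's expectation of information on local host defence. The primary outcome is not affected.

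**Working it through.** The protocol states no figure for peritonitis, so there is none to reproduce. The steps below take cohort size, follow-up and drop-out from the document and assume the rest.

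**Inputs from the protocol (Sample size estimation).** 60 children, 10 months, 50% drop-out.

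**Assumed.** Exits spread at a constant hazard; an episode rate r of 0.4 to 1.0 per patient-year; a proportion q of 10 to 50% of episodes ending study treatment; between-child variation in risk (gamma frailty) with variance 0 or 1.

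**Step 1: exposure.** The hazard of exit is ln 2 / 10 = 0.0693 per month.
- All children: 60 × 0.5 / 0.0693 = 433 patient-months, or 36.1 patient-years.
- Completers: 30 × 10 = 300 patient-months, or 25 patient-years.
- Share of exposure in completers: 25 / 36.1 = 69%. So 31% of the time at risk is lost even if no episode ever ends treatment.

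**Step 2: episodes expected in all treated children.** r × 36.1 gives 14 at 0.4 per year, 25 at 0.7 and 36 at 1.0. Frailty lowers these slightly.

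**Step 3: episodes left to the completer ANOVA.** Without frailty, completers contribute r × (1 − q) × 25 episodes, so the share kept is 0.693 × (1 − q).

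| q | Share kept | Share lost |
|---|---|---|
| 10% | 62% | 38% |
| 20% | 55% | 45% |
| 40% | 42% | 58% |
| 50% | 35% | 65% |

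Simulation agrees for q of 10 to 40% (38 to 59% lost without frailty, 38 to 63% with it). With frailty variance 1 and q = 50%, completers hold 5.3 of 16.6 episodes at 0.5 per year and 7.9 of 25.8 at 0.8 per year, so 68 to 69% are lost. The overall range is roughly 40 to 70%.

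**Step 4: the completer rate.** Without frailty it is r × (1 − q). At a true 0.70 per year it reads 0.63, 0.56 and 0.42 for q of 10, 20 and 40%.

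**Step 5: the ratio between arms.** The completer ratio is the true ratio multiplied by (1 − q₁)/(1 − q₂). If q is the same in both arms, the factor is 1 and the ratio is undistorted in this simple model. Distortion needs q to differ by arm, and nothing in the protocol says that it does.

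**Step 6: episodes left to first-event Kaplan-Meier.** Without frailty, the expected number of first episodes is 60 × r × [1 − exp(−(r + h)T)] / (r + h). Here T = 10/12 year, and h is the hazard of other exits, 0.832 − rq per year. At r = 0.7 and q = 20%, h = 0.692 and the result is 20.7 of 25.2 episodes, so 18% are repeats and go uncounted. Simulation over r of 0.4 to 1.0 and q of 10 to 40%, with and without frailty, gives 8 to 38%. Taking q to 50% at r = 0.4 without frailty moves the lower end only to 7%.

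**Step 7: precision.** With D episodes split evenly between arms, the 95% interval for the rate ratio runs from the estimate divided by, to the estimate multiplied by, exp(1.96 × √(4/D)) under a Poisson model. D = 15 gives a factor of 2.75 and D = 35 gives 1.94. At r = 0.7 and q = 20%, all 25 episodes give 2.19 and the 14 in completers give 2.85. Overdispersion would widen all of these.

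**The case against.** The closing sentence reads as a general one, in an article that condenses a fuller protocol. It fits the serially measured secondary variables (CA-125, VEGF, TGF-β, IL-6, blood gases), and the authors may never have meant it for peritonitis. The body of the article says incidence, and time to first episode in all treated children does address incidence with proper use of time at risk. Only the abstract says rates. This shows that the mismatch may be unintended. It does not remove it: the sentence covers secondary variables without exception, and the abstract's promise has no method behind it.

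Peritonitis may also be a minor cause of exit. The abstract's Background does speak of "limited technique survival due to infections and progressive ultrafiltration failure", but the main Background section says infectious PD failure is becoming less common, and the sample size section names transplantation first among the reasons for drop-out. This stands, and it makes the upper assumptions doubtful. At 1.0 episode per year with 40% ending treatment, 36.1 × 0.4 = 14.4 of the 30 exits would be due to peritonitis. The lower end is easier to square with the text, and there the completer analysis still loses about 38%.

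A reader might infer that treatment-ending episodes disappear from the trial's results altogether. They do not: Kaplan-Meier takes everyone who started, so a treatment-ending first episode counts there. Nor are repeats lost everywhere, since an ANOVA of episode counts could include them, though only in completers. A reader might also infer a biased treatment comparison from the low completer rate. Step 5 shows that this does not follow.

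Finally, no method makes so few episodes very informative. That is true, and it limits the gain from the fix.

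**Conclusion.** The point holds as a mismatch between a stated rule and one of the outcomes it covers. Followed as written, the protocol would not produce the peritonitis rate that its abstract announces, and no single analysis would use every episode in every treated child. The Statistical approach section and the abstract need to be reconciled.

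The size depends wholly on assumed episode rates, exit proportions and between-child variation. Over the ranges used, the completer analysis forgoes roughly 40 to 70% of episodes and first-event Kaplan-Meier about 8 to 38%. The firmest figure is the 31% of exposure outside completers, which needs only the protocol's own drop-out and evenly spread exits. Understatement of the completer rate follows if any episodes end treatment. Bias in the ratio between arms is not established. Because this is a secondary outcome and the change is cheap, it should be made, but it does not threaten the primary result.

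**What to change.** In Statistical approach, exempt peritonitis from the sentence on secondary variables and state the following.

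- Count all episodes, including any that leads to exit, in all patients started on study medication. This is the population already used for Kaplan-Meier, and it keeps time on study fluid defined for everyone analysed.
- Report episodes per patient-year by arm, and the rate ratio with 95% confidence interval. Use either a Poisson model with standard errors robust to overdispersion or a negative binomial model, with log time on study fluid as offset.
- Describe severity over all episodes in all treated patients, allowing for clustering by child.
- Keep time to first episode as a supportive analysis.

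The cost is a few lines of text and no new data: adverse events, peritonitis included, and the clinical course of peritonitis are already to be recorded. The drawback is limited precision. With about 15 to 35 episodes the interval will be wide under any method, and an overdispersion parameter would be poorly estimated, so the model should be kept simple.
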